## Abstract

**Background:**

Post-traumatic stress disorder (PTSD) remains a significant treatment challenge among Canadian veterans. Currently accessible pharmacological and non-pharmacological interventions for PTSD often do not lead to resolution of PTSD as a categorical diagnosis and have significant non-response rates. Sudarshan Kriya Yoga (SKY), a complementary and integrative health (CIH) intervention, can improve symptoms of PTSD. In response to the COVID-19 pandemic, this intervention has pivoted to virtual delivery and may be reaching new sets of participants who face multiple barriers to care.

**Objective:**

To evaluate the implementation and effectiveness of virtually delivered Sudarshan Kriya Yoga (SKY) on decreasing PTSD symptom severity, symptoms of depression, anxiety, and pain, and improving quality of life in Canadian veterans affected by PTSD.

**Methods and analysis:**

Using a mixed-methods approach guided by the RE-AIM framework, we will conduct a hybrid type II effectiveness and implementation study of virtually delivered Sudarshan Kriya Yoga (SKY) for Canadian veterans. Effectiveness will be evaluated by comparing virtually delivered SKY to a waitlist control in a single-blinded (investigator and data analyst) randomized controlled trial (RCT). Change in PTSD symptoms (PCL-5) is the primary outcome and quality of life (SF-36), symptoms of depression (PHQ-9), anxiety (GAD-7), and pain (BPI) are secondary outcomes. The SKY intervention will be conducted over a 6-week period with assessments at baseline, 6-weeks, 12-weeks, and 30 weeks. The reach, effectiveness, adoption, implementation, and maintenance of the intervention will be evaluated through one-on-one semi-structured interviews with RCT participants, SKY instructors, health professionals, and administrators that work with veterans.

**Discussion:**

This is the first investigation of the virtual delivery of SKY for PTSD in veterans and aims to determine if the intervention is effective and implementable at scale.

## Introduction

Post-traumatic stress disorder (PTSD) was originally identified among soldiers who experienced horrific events on the battlefield [1]. The symptoms of PTSD include, but are not limited to, intrusive recollections including flashbacks, avoidance of reminders of the trauma, alterations in mood or cognition, and hyperarousal [2]. Besides many physical and psychological symptoms associated with PTSD, significant disruption in social and/or occupational functioning can also occur.

PTSD is highly prevalent among Canadian veterans. According to Veterans Affairs Canada (VAC), of the 133,200 veterans receiving benefits from VAC, 24,538 (18.4%) are diagnosed with and receive disability benefits for PTSD. In addition, the prevalence of PTSD among Canadian veterans is rising, indicating that the number of veterans in need of support for PTSD will likely continue to increase over time [3]. Due to various barriers including long wait times, stigma, and uncertain or fragmented financial coverage [4], a significant proportion of veterans may not receive effective treatment for their PTSD.

PTSD is highly comorbid with other psychiatric and physical illnesses, including major depressive disorder (61.5%), generalized anxiety disorder (52.3%), and chronic pain (50%) [5–7]. These comorbidities have significant consequences. Individuals who have both PTSD and depression are more likely to engage in purposeful self-harming behaviors [8]. Additionally, those with comorbid PTSD and social anxiety disorder are more than 3 times more likely than those with PTSD alone to report a past suicide attempt [9].

There are a variety of interventions available for PTSD, with trauma-focused cognitive-behavioral therapies (TF-CBT) demonstrating the largest benefit compared to a control in clinical trials with a standardized mean difference (SMD) of 1.23 (95% CI [0.97, 1.50]) [10–12]. Although trauma-focused psychotherapy has larger effects, pharmacotherapy is also recommended as first-line treatment when trauma-focused psychotherapy is not available or not preferred by the patient [11]. First-line pharmacotherapies include selective serotonin reuptake inhibitors (SSRIs) such as fluoxetine, paroxetine, and sertraline, and the serotonin-norepinephrine reuptake inhibitor (SNRI), venlafaxine [13].

Despite this evidence for efficacy, there remain several treatment challenges with current PTSD therapies. Firstly, treatments often do not lead to resolution of PTSD as a categorical diagnosis and even the most effective trauma-focused therapies have non-response rates as high as 50% [10, 14]. Secondly, pooled data from randomized controlled trials (RCTs) demonstrate that dropout rates are higher for trauma-focused therapies compared to non-trauma-focused therapies, at 18% and 14%, respectively [14, 15]. While the reasons for attrition are not fully known, stigma, confidentiality concerns, significant time demands, therapist fit, and negative expectancy likely play important roles [4]. Thirdly, existing therapies have reduced effectiveness and lower treatment retention in veteran populations compared to civilians [16]. There is thus an evident need for versatile treatments for PTSD and its comorbidities.

The COVID-19 pandemic has exacerbated existing challenges of access to appropriate care [17]. Virtual therapies, in particular telepsychotherapies, have enabled mental health professionals to continue supporting individuals throughout the pandemic. As virtual therapies become more common, research must also focus on implementation in addition to effectiveness to support real-world uptake of interventions. Recent research has shown high acceptance of virtual therapies among veteran populations, while also identifying several barriers, facilitators, and future challenges [18–20]. Barriers can include poor access to high-speed internet, lack of privacy in the home, lack of comfort with technology, and a lack of personal connection with therapists that can be perpetuated with decreased non-verbal cues. Facilitators can include the convenience of using virtual therapies, the comfort of being in one’s home, reduced travel time, and reduced costs due to missed work [19].

In Canada, the use of complementary and integrative health (CIH) interventions has increased steadily over the last several decades; including CIH interventions for PTSD [21]. The rise of CIH interventions among individuals with PTSD may in part be a response to existing challenges of efficacy and accessibility of PTSD treatments [14, 19]. Among veterans in particular, there has been growing interest in CIH interventions [22], with almost 50% of veterans and active duty personnel using at least one CIH therapy [23]. Promising results for meditation and mindfulness-based interventions have been demonstrated for PTSD and many of its comorbidities. Additionally, these interventions have the added benefit of a strong safety profile [24–26].

CIH interventions are complex interventions that involve numerous components such as meditation and breathing exercises, psychoeducation, and group dynamics [27]. Successful implementation of these practices into new contexts and settings necessitates understanding the perspectives of involved stakeholders, including Canadian veterans, instructors, health professionals, and administrators that work with veterans. The availability of resources, administrative and bureaucratic difficulties with integrating CIH interventions in routine care, and balancing patient preferences are among some of the challenges that stakeholders must consider when implementing CIH therapies into veteran health care [28].

Several CIH interventions have demonstrated therapeutic efficacy for improving PTSD symptoms [29–33]. Over the last decade, numerous studies have demonstrated the effectiveness of Sudarshan Kriya Yoga (SKY), a form of breathing-based meditation, for improving PTSD in veteran populations [29, 34–36]. A recently published RCT suggested non-inferiority of SKY compared to cognitive processing therapy for improving PTSD symptoms in US military veterans [37]. Compared to a waitlist control, SKY has shown an effect size of 1.16 for improvement of PTSD symptoms (95% CI [0.20, 2.04]) [29] with retention rates between 81% and 95% [29, 38]. The beneficial effects of SKY are not limited to PTSD, but extend also to major depressive disorder and generalized anxiety disorder [39, 40].

Outside of research settings, SKY is being delivered widely in the United States for combat and non-combat veterans, as well as their families and caregivers. It is taught by highly trained and certified instructors from the International Association for Human Values and Art of Living Foundation. By shifting responsibility for intervention delivery to expert, non-healthcare professionals, SKY may provide a pathway to increase intervention accessibility alongside formal healthcare delivery. SKY is typically delivered to groups of 8–12 people by certified instructors. In response to the pandemic, this intervention has pivoted to virtual delivery. Informal evaluative reports from participants and SKY instructors [personal communication] suggest that virtual delivery creates a similar participant experience of a safe, non-judgemental community of learning, engagement and change. Reports from instructors also suggest that the SKY intervention has reached new sets of participants, including those who suffer from social anxiety or live in rural settings and face geographic barriers to care.

The existing evidence supporting the use of SKY for veterans with PTSD provides the rationale for studying virtually-delivered SKY in Canadian veterans with PTSD. There is a need for high quality-controlled trials in order to generate evidence in a Canadian context for the effectiveness of SKY and to better understand how such an intervention should be implemented.

This protocol article describes the research study “Sudarshan Kriya Yoga (SKY) for Canadian veterans with PTSD: a nation-wide effectiveness and implementation evaluation”. This trial protocol was developed through extensive and iterative consultation with Canadian veterans with lived experience with PTSD, family members of veterans, experts at specialty veteran mental health clinics across Canada, and experts in SKY delivery within the context of research trials. These consultations were conducted to help ensure relevance of the trial to Canadian veterans living with PTSD and feasibility of the trial within the particularities of the contemporary Canadian context. This article describes the procedures, methodology and methods, besides other considerations for a hybrid type II study design of a virtually-delivered meditation intervention.

### Study aim and objectives

The aim of this study is to evaluate the effectiveness and implementation of the virtually-delivered SKY (v-SKY) intervention for Canadian military and RCMP veterans living with PTSD. PTSD symptom severity and several health-related outcomes will be evaluated for effectiveness. The implementation of the v-SKY intervention will also be evaluated by interviewing RCT participants, SKY instructors, health professionals, and administrators that work with veterans. Evaluating implementation of a virtual intervention is relevant in both pandemic and post-pandemic contexts where virtual interventions will likely continue to be widely available and possibly preferred by patients and providers.

The protocol for the effectiveness trial is reported using the Standard Protocol Items: Recommendations for Interventional Trials (SPIRIT) statement [41] and the intervention is described using the Template for Intervention Description and Replication (TIDieR) checklist and guide as well as the CheckList stAndardising the Reporting of Interventions For Yoga (CLARIFY) [42, 43]. The protocol for the implementation evaluation is described according to the Standards for Reporting Implementation Studies (StaRI) statement [44]. A completed SPIRIT table showing the timeline for this study is shown in **Table 1** and a completed SPIRIT Checklist is located in **Section 1 of the S1 Appendix**. The completed World Health Organization Trial Registration Data Set can be found in **Section 2 of the S1 Appendix**.

**Table 1 pone.0275774.t001:** Outline of enrolment, study intervention, and effectiveness and implementation evaluations.

Timeline	Pre-study Screening	Screening/Consent	Randomization/Allocation	T1	*Weeks 1–6*	T2	*Weeks 6–12*	T3	T4
				Baseline					
				*Week 0*		*Week 6*		*Week 12*	*Week 30*
**Enrolment**									
Informed Consent Form		X							
Pre-screener script	X								
PCL-5		X					X		
Randomization			X						
MINI		X							
MoCA Mini		X							
**Intervention**									
SKY Intervention–Active (ACT) group					X				
SKY Intervention–wait list control (WLC) group							X		
Attendance logs					X		X		
**Assessments**									
Intake questionnaire				X					
PCL-5				X		X		X	X
CAPS-5				X					
PHQ-9				X		X		X	X
GAD-7				X		X		X	X
BPI				X		X		X	X
SF-36				X		X		X	X
Medication History				X		X		X	X
**Implementation Evaluation**									
Post-intervention questionnaire						X (ACT group)		X (WLC group)	
**Timeline**	After T3 assessment			After completion of last cohort			Post study		
Qualitative interviews–RCT participants	Participants will be identified		X	X					
Qualitative interviews–Stakeholder participants	Participants will be identified					X	X		
Qualitative interviews–Instructor participants	Participants will be identified					X	X		

Abbreviations: PTSD Checklist for DSM-5 (PCL-5), Mini International Neuropsychiatric Interview (MINI), Montreal Cognitive Assessment mini version (MoCA Mini), Clinician Administered PTSD Symptom Scale (CAPS-5), Patient Health Questionnaire-9 (PHQ-9), Generalized Anxiety Disorder Scale (GAD-7), Brief Pain Inventory (BPI), Health-Related Quality of Life measurement (SF-36)

#### Primary objectives

*Effectiveness evaluation*. In Canadian veterans with clinically significant PTSD symptoms, we will estimate the short-term (6-weeks) effectiveness of v-SKY compared to a waitlist control at reducing PTSD symptoms as measured by PTSD Checklist for DSM-5 (PCL-5).

*Implementation evaluation*. We will explore adoption of v-SKY by examining the intervention’s acceptability, accessibility, and perceived effects amongst Canadian veterans with PTSD and amongst health professionals, and administrators that work with Canadian veterans.

#### Exploratory objectives

We will estimate the short- and long-term effects of v-SKY on quality of life, depression, anxiety, and chronic pain in Canadian veterans affected by PTSD. In addition, we will evaluate the reach, adoption, implementation, and maintenance of the v-SKY intervention amongst Canadian veterans with PTSD, SKY instructors, and the health professionals, and administrators that work with veterans.

## Materials and methods

### Overall research design

We will conduct a hybrid type II effectiveness and implementation evaluation guided by the RE-AIM framework [45]. RE-AIM provides a framework for measuring the success of translating findings from effectiveness research into practice by evaluating *effectiveness* along with the *reach*, *adoption*, *implementation*, and *maintenance* of an intervention on an individual and organizational level. The RE-AIM framework facilitates the study of an intervention under more complex, real-world conditions as opposed to optimized and controlled conditions typical of trials aiming to maximize internal validity [45].

### Trial design

Effectiveness will be evaluated with a randomized, waitlist controlled, single-blinded (investigator and data analyst), cross-country trial conducted remotely using video calls with a primary endpoint of changes in PTSD symptom severity. Randomization will be performed with a 1:1 allocation to either the active intervention or waitlist control group. This study will be conducted out of the Sinai Health System together with the Atlas Institute for Veterans and Families, with study promotion and recruitment support from several clinical and community-based organizations across the country. Evaluations of PTSD symptom severity, depression, anxiety, pain, and quality of life will be administered at baseline, 6-weeks, 12-weeks, and 30-weeks follow-ups (**Fig 1)**.

**Fig 1 pone.0275774.g001:**
[figure not shown]
Flowchart showing the timeline of the randomized controlled trial.

This study was originally conceived as a comparative effectiveness study using a non-inferiority approach, similar to the US study described by Mathersul et al [37, 46]. This proposed trial would have compared virtually-delivered SKY (v-SKY) to virtually-delivered cognitive processing therapy (CPT) in a non-inferiority trial, with the key innovation being virtual delivery of SKY. However, formal consultation with experts in veteran mental health care and veterans who have lived experience with PTSD indicated that the SKY intervention would likely be most useful in a Canadian context if it were to be integrated into the current treatment environment instead of being compared to a standard of care treatment. For instance, many patients in specialty clinics have not responded to existing treatments, which emphasized a need for more complementary therapeutic options. These discussions also identified wait times for access to care between 4–8 weeks, which is comparable to the wait list control time period. Likewise, as per our earlier estimates, a high number of veterans with PTSD may not be actively receiving treatment for their illness. Thus, a wait list control design was considered as the most appropriate, relevant, and feasible.

Several RCTs of SKY for veterans living with PTSD have been conducted using waitlist control designs including in the United States [29] and Australia [38]. Using a waitlist control design encompasses using a control group that is not actively receiving treatment for their illness during the intervention period. Baseline assessments will be conducted with the active intervention (ACT) and waitlist control (WLC) groups before the active intervention group receives the intervention. After the 6-week intervention period for the ACT group, there will be a 2-week data collection period for both the ACT and WLC groups. After this 2-week period, the WLC group will begin the intervention for 6-weeks and the ACT group will not. After the WLC group’s 6-week intervention, there will also be a 2-week data collection period for both groups.

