#### Randomization and allocation

Participants will undergo 1:1 randomization and allocation to the active v-SKY intervention group or a waitlist control (WLC) group using the data management and randomization services available at Sinai Health System. This will be used as a central repository for the generation of randomization codes and will ensure concealment of randomization. A member of the research team not involved in recruitment or evaluations will contact participants with randomization and allocation information to maintain blinding. Participants will be allocated into either the active or WLC arms of cohorts that will be running on a rolling basis. Participants randomized to the active arm will receive the v-SKY intervention in groups of 8–12. Participants allocated to the WLC arm will receive the v-SKY intervention after a waitlist period of approximately 6 weeks. It will not be possible for participants to be blinded to their intervention status, but they will be instructed to not share allocation information with study staff. Separate groups for Francophone speakers will be delivered in French on a rolling basis.

*Trial intervention*. SKY meditation is a standardized intervention that includes relaxation techniques as well as periods of group discussion [34, 46]. This practice incorporates different breathing techniques centered around controlling arousal and attention. Initially, the breathing techniques that are taught are calming and focusing. While progressing through the sessions, breathing exercises are more engaging and energizing, which allows the practitioner to focus more in each moment. Participants will be encouraged to learn all of the techniques that are covered during these sessions and also utilize the techniques that are most appropriate for their personal needs. After some initial training sessions, participants will be encouraged to practice their new SKY techniques in environments and situations that they have been avoiding. They would begin with situations that are less triggering, and progress to more difficult situations. At each group session, participants will describe their experiences and discuss ways to continue to incorporate the SKY techniques into their daily lives, until it reaches a point of being natural to use these skills throughout the day, both in practice, and in application.

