#### Outcome measures and assessments

For the effectiveness trial, change in PTSD symptoms is the primary outcome measure (**Table 4**). Changes in depressive, pain, anxiety symptoms and quality of life are exploratory outcome measures.

**Table 4 pone.0275774.t004:** Primary and exploratory outcome measures for the effectiveness evaluation.

Outcome Measure	Explanation
Change in PTSD symptoms *Primary*: Change in PCL-5 scores from baseline to post-treatment (6-weeks).	The PCL-5 is a well-validated, widely used, and easy to administer 20-item self-report scale that is widely used in PTSD research and clinical practice [47]. Responses to each item relate to the four symptom clusters for PTSD, for which separate scores can be measured and used for additional analyses. The PCL-5 will be used for follow-up assessments over the CAPS-5 because of the feasibility of a self-report measure over a semi-structured interview and to reduce the reporting burden on participants.
*Exploratory*: Prolonged changes in PCL-5 scores from baseline to 12-week follow-up and 30-week follow-up.	
Change in depressive symptoms *Exploratory*: Change in depressive symptoms as measured by the nine-item Patient Health Questionnaire (PHQ-9) scores from baseline to 6-weeks, 12-weeks, and 30-weeks follow-ups.	PHQ-9 is a well-validated and widely used self-report scale used in depression research. Each item is rated on a 4-point scale for how much it bothered the participant in the past 2 weeks. A self-report scale is more feasible than an assessor-rated scale (e.g. HAM-D17) given the virtual nature of this study.
Change in pain symptoms *Exploratory*: Change in pain symptoms as measured by the Brief Pain Inventory (BPI) from baseline to 6-weeks, 12-weeks, and 30-weeks follow-ups.	BPI is a validated self-report scale used in pain trials and clinical pain practice and is a core outcome measure per the Initiative on Methods, Measurement, and Pain Assessment in Clinical Trials (IMMPACT) recommendations [50]. Two independent and clinically relevant measures are included: pain severity and pain interference with function.

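### Table 1 schedules the self-reported T1 baseline PCL-5 after allocation, and nothing requires it to be completed before participants learn their arm

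*Protocol article*

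**What the plan says.** **Order of events.** In Table 1 (Study aim and objectives) the consecutive column headings read "Randomization/Allocation T1", and T1 is labelled as the Week 0 baseline. The randomization mark stands in its own column, ahead of T1. PCL-5, PHQ-9, GAD-7, BPI and SF-36 are all marked at T1. A separate PCL-5, used for eligibility, is marked at screening in the Enrolment block, before randomization.

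**Text on baseline.** The Trial design section says: "Baseline assessments will be conducted with the active intervention (ACT) and waitlist control (WLC) groups before the active intervention group receives the intervention".

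**Knowledge of the arm.** Under Randomization and allocation, a team member who takes no part in recruitment or evaluation "will contact participants with randomization and allocation information to maintain blinding". The same section says: "It will not be possible for participants to be blinded to their intervention status". Participants are asked not to reveal their arm to study staff. The blinded roles named in the Trial design section are the investigator and the data analyst.

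**Use of the T1 score.** Table 4 describes the PCL-5 as a self-report scale and defines the primary outcome as its change from baseline to 6 weeks. The Effectiveness part of the Data analysis section compares the arms with adjustment for baseline measures. It also compares baseline severity between arms and adjusts for differences found significant.

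**The concern.** A baseline covariate is safe to adjust for because allocation cannot have affected it. That protection is lost if the participant knows the arm when filling in the form. A veteran who has just been told to wait, or has just been offered the course at once, may rate symptoms differently. Blinding the staff does not help, because the participant is the rater.

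The T1 PCL-5 feeds the primary result both as reference point and as covariate. If knowing the arm did produce a difference at T1, the planned comparison of baseline severity would treat it as a chance imbalance and adjust for it. A larger sample would not reduce such a bias, and an analysis plan could not restore a T1 score already affected. The order of these steps is trial conduct, which the article itself sets out.

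**Working it through.** **Step 1: what fixes the order.** The Trial design sentence alone places T1 before treatment; it does not place T1 relative to randomization or disclosure. Table 1 puts T1 after allocation. Because the screening PCL-5 is listed separately, T1 is a distinct, later assessment. The article gives no time for the contact that discloses the arm. So allocation before T1 is stated, disclosure before T1 is possible, and nothing rules it out.

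**Step 2: the yardstick.** The sample size section gives 80% power, 5% type I error, SD 11, a difference of 5, and 76 per group. Taking 5 as PCL-5 points and a two-sided test:

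n = 2 × (1.96 + 0.8416)² × (11/5)² = 2 × 7.849 × 4.84 = 75.98, so 76 per group, as stated.

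The 5-point target is therefore a fair yardstick. With 100 per group and the stated 25% dropout, 75 per group remain.

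**Step 3: the bias formula.** Let Y be the mean PCL-5 at T2, B the mean at T1, and β the baseline slope.

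Adjusted difference = (Y_ACT − Y_WLC) − β × (B_ACT − B_WLC)

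Analysing change with baseline as covariate gives the same expression. If knowing the arm shifts reported T1 scores by s points between arms and leaves T2 untouched, the bias has size β × s. Lower scores are better. If waitlisted participants score higher at T1, the estimate moves against v-SKY; if they score lower, it moves in favour of v-SKY.

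**Step 4: illustration.** β and s are assumptions, because the article gives neither; s = 0 is included because nothing shows that a shift occurs. For the type I error I also assume SD 11 at both visits (so that β equals the correlation), 75 per arm and a two-sided 5% test:

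SE = 11 × √(1 − β²) × √(2/75), which is 1.56 for β = 0.5 and 1.28 for β = 0.7

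Type I error = 1 − Φ(1.96 − βs/SE) + Φ(−1.96 − βs/SE)

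| s (points) | Bias, β = 0.5 | Type I error | Bias, β = 0.7 | Type I error |
|---|---|---|---|---|
| 0 | 0 | 5.0% | 0 | 5.0% |
| 1 | 0.5 | 6.2% | 0.7 | 8.5% |
| 2 | 1.0 | 9.9% | 1.4 | 19.4% |
| 3 | 1.5 | 16.1% | 2.1 | 37.4% |

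The bias runs from 0 to 2.1 points, and 2.1/5 = 42% of the target difference at the top of the assumed range.

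**The case against.** The strongest reply is that harm needs disclosure, not merely allocation. A code may be generated and withheld until T1 is done, and the article does not say when participants are told. Naming the two groups in the baseline sentence may be shorthand. The flowchart (Fig 1) and the full protocol are not available here and may settle the order. T1 also precedes treatment in both arms, and a pre-randomization PCL-5 already exists. All of this stands, and it limits the point to an unprotected step; it does not establish an actual contamination. It does not remove the point, because the published schedule puts allocation first and states no safeguard.

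A reader might infer three stronger things that the document does not support:

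- **That T1 is collected from people who know their arm, so the primary estimate is biased.** The timing of disclosure is not stated, and no shift is shown.
- **That the bias is the full shift, 1 to 3 points or 20 to 60% of the target.** That would hold for an unadjusted change score, but the planned comparison adjusts for baseline.
- **That anyone lost between allocation and T1 drops out of the analysis.** The Effectiveness section says that everyone randomized is included, and handling of a missing baseline is commonly left to the analysis plan.

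The formula also assumes that a reaction to allocation is confined to T1. If it lasts to T2, the net effect differs. T2 remains an unblinded self-report whatever is done about T1.

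**Conclusion.** The concern holds as an avoidable exposure of the primary estimate. As scheduled, the T1 PCL-5 comes after allocation, participants cannot be blinded, and nothing ensures that they complete it before learning their arm. The score may therefore carry knowledge of the arm into both the change score and the covariate.

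The size and direction are unknown. The range of 0 to 2.1 points rests wholly on an assumed slope of 0.5 to 0.7 and an assumed differential shift of 0 to 3 points at T1 only. It shows what could be at stake and is not an estimate of what will happen. Adjusting for baseline makes the bias smaller than the shift itself but does not remove it.

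**What to change.** - **Order.** Complete the T1 self-report measures (PCL-5, PHQ-9, GAD-7, BPI, SF-36) before randomization or, at minimum, before the arm is disclosed to the participant. Reorder Table 1 and amend the Trial design and allocation text to say so. If this is already the practice, correcting the text is enough.
- **Participants already enrolled.** For anyone who completed T1 after learning the arm, or who has no T1, use the pre-randomization screening PCL-5 as the baseline covariate, at least in a sensitivity analysis.

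**Cost.** No new assessment and no change in sample size. If T1 moves ahead of randomization, a few people will complete it and then not be randomized, and the gap between baseline and Week 0 may lengthen while groups of 8 to 12 fill. Delaying disclosure only, with randomization left where it is, avoids that longer gap. The screening score is truncated by the entry criterion (>38), so it is likely to be slightly less predictive than T1, but the truncation applies equally to both arms.
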